### Interim analyses {21b}

N/A: As this is a low-risk behavioral intervention study, there are no plans to conduct interim efficacy or safety analyses.

### Methods for additional analyses (e.g., subgroup analyses) {20b}

All analyses are described in Sect. 20a, including subgroup analyses.

### Methods in analysis to handle protocol non-adherence and any statistical methods to handle missing data {20c}

As described in Sect. 19, study coordinators will monitor for missing data and follow up with participants when missing data are identified. As described in Sect. 20a, any missing values will be handled with well-established statistical methods, including multiple imputation, full information, or empirical Bayes estimation, or MICE.

### Plans to give access to the full protocol, participant-level data, and statistical code {31c}

The study protocol and any datasets or statistical code required to support the protocol will be supplied on request. We will also make de-identified datasets available via a public data repository (see Sect. 29).

## Oversight and monitoring

### Composition of the coordinating center and trial steering committee {5d}

N/A: This project does not include committees who are involved in trial coordination or conduct. Roles and responsibilities of study staff are outlined under “Authors’ contributions.”

### Composition of the data monitoring committee, its role and reporting structure {21a}

N/A: A data monitoring committee is not needed, as the study sponsor deemed the study as requiring only a local Safety Monitoring Committee, which we describe below in Sect. 22.

### Adverse event reporting and harms {22}

This study has been designated as minimal risk by the Seattle Children’s Institutional Review Board. Monitoring study safety will occur from the initial screening, throughout the informed consent process, and through study completion under the principal investigators’ ([name]/[name]) supervision. A Safety Monitoring Committee (SMC) consisting of two independent investigators will review study progress and recommend appropriate action regarding adverse events or other safety issues.

In the case of an adverse event believed to be related to the study, documentation will be collected to describe the nature of the event and any associated risks. All adverse events will be discussed at weekly study meetings, and event reports will be provided to the SMC for quarterly review. The PIs will comply with all requirements of the IRB for the reporting of safety data and adverse/serious adverse events. All serious and/or unexpected problems presumed to be related to the study will be reported by the PIs to the IRB, the SMC, and the funding organization within 5 days after discovery. [name] or [name] will retain the authority to stop or modify the trial at any time. All actions taken will be documented on a case report form.

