##### Social learning and cognitive behavioral therapy (SLCBT) condition

Participants assigned to the SLCBT group will complete a 4-week web-based intervention. The website includes an introductory module, three skills-training modules (i.e., strategies to promote wellness behaviors, use adaptive cognitive coping, model wellness behaviors for their children, and determine when it is appropriate to take further action regarding potential illness in their child), and a brief maintenance and summary module. The web modules were designed to be visually attractive and interactive in order to engage participants through using brief questions to assess participant knowledge, interactive question/answer components, instructional videos, and storyboards that participants can click through. Screenshots can be seen in Fig. 3. Additionally, participants are provided a “Toolbox” in which informational handouts can be accessed, downloaded, and printed. The handouts provide a summary of the knowledge provided in each module. Participants in each group are instructed to log in to the website for 3–4 weeks, approximately 20–30 min per week. Research team members will regularly assess web program usage for all participants and will send reminders up to two times each week as needed to encourage regular usage and completion of all modules.

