### Provisions for post-trial care {30}

Adverse events are not expected, however, if they occur they are expected to be minor. Therefore, there are no provisions for any additional post-trial care or to provide compensation to those who suffer harm from trial participation.

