***Demographics and background measures***							
Demographics form	Demographic questionnaire to report on parent and child sex, gender, race, and ethnicity; family income; and parent education	P/C	X				
Medical history	Parent medical, psychiatric, and surgical history (including chronic conditions and chronic pain) and child medical diagnoses (including abdominal pain)	P/C	X	X	X	X	X
Irritable Bowel Syndrome Symptom Severity Scale (IBS-SSS) [47]	5-item measure which assesses parent severity and frequency of abdominal pain, bloating severity, dissatisfaction with bowel habits, and the impact of these symptoms on everyday activities	P/C	X	X	X	X	X
Daily Parenting Hassles Scale [48–50]	20-item scale that assesses parent burden in meeting the needs of their children and troublesome behavior of children. Subscales include challenging behavior and parenting tasks	P/C	X				

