Aim 3: Determine cost savings of implementing this preventive intervention on health care expenditures and resource utilization over 18 months. To assess hypothesis 5 (that the SLCBT group will demonstrate cost savings in relation to the EC group), we will first estimate total health care costs in each group, which will be the sum of direct medical costs, direct non-medical costs, and indirect costs. Direct medical costs for each group will be estimated by multiplying utilization estimates for each reported service by the service-specific unit cost from the most recent Medical Expenditure Panel Survey (MEPS) [67], and then summing the costs of all services used. Direct non-medical costs for each arm will be the sum of parent-reported out-of-pocket expenses for special foods, equipment, and transportation to medical appointments. Indirect costs for each arm will be estimated by multiplying parent-reported hours of missed work and leisure time due to caring for their child (i.e., when absent from school due to illness behavior, taking to medical appointments) by the current mean hourly wage for a US worker from the Consumer Price Index of the US Bureau of Labor Statistics [68]. Cost superiority will be indicated by the arm with lower total health care costs if arms are equal in size, or by the average health care cost per family if they are not. Should the SLCBT arm prove superior as hypothesized, intervention-related cost savings per family will be estimated as the difference in average health care costs per family (health care cost/familySLCBT − health care cost/familyEC).

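### The harms section makes adverse-event documentation depend on believed relatedness yet refers to all adverse events; reconcile the two, and show by-arm child diagnoses and service use beside the Aim 3 cost result

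*Protocol article*

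**What the plan says.** In the protocol article, Adverse event reporting and harms {22} contains three statements that bear on this point.

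- Documentation: "In the case of an adverse event believed to be related to the study, documentation will be collected".
- Review: "All adverse events will be discussed at weekly study meetings, and event reports will be provided to the SMC for quarterly review".
- Expedited reporting: "All serious and/or unexpected problems presumed to be related to the study will be reported by the PIs to the IRB", and also to the safety monitoring committee and the funder, within 5 days of discovery.

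Provisions for post-trial care {30} gives the prior expectation: "Adverse events are not expected, however, if they occur they are expected to be minor". Interim analyses {21b} plans no interim look at safety.

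The SLCBT arm trains parents, among other skills, to "determine when it is appropriate to take further action regarding potential illness in their child". In Analyses by aims, Aim 3 sums medical, non-medical and indirect costs and sets the rule: "Cost superiority will be indicated by the arm with lower total health care costs". If the arms differ in size, the average cost per family is compared instead.

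**The concern.** The trial tries to change how parents respond to a child's complaints and expects health care use to fall. Background and rationale {6a} counts reacting too little, as well as too much, as inappropriate illness behavior. A possible unwanted effect is therefore that a real illness is recognised late. The documents do not show that this will happen, but the trial should be able to look for it.

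Two things stand in the way. The harms section makes written documentation follow a judgement of relatedness, in tension with its own next sentence. And the cost analysis treats less care as good whatever care it was. At stake is whether the safety monitoring committee could notice an imbalance between the arms, and whether a reader of the Aim 3 result could tell a saving on unnecessary visits from care that was needed and not sought.

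**Working it through.** No figure in the plan is in dispute and no calculation is needed. The check sets the relevant sections side by side.

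1. **Scope of each step in {22}.** Documentation covers events believed related. Weekly discussion covers all adverse events. The quarterly committee review covers event reports, without saying which events generate one. Five-day reporting covers serious or unexpected problems presumed related.

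2. **Two readings.**
   - If documentation is a condition of entry, the event reports reaching the committee have already passed a relatedness judgement, and the reference to all adverse events cannot be met in full.
   - If related events merely receive a fuller description, the section never says what record the other events receive.
   - On either reading, the handling of an event judged unrelated is not settled.

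3. **Who judges.** The article does not say. Who will be blinded {17a} and Procedure for unblinding {17b} state that coordinators know the allocation, and they are in contact with participants. The judgement may therefore be made, or informed, by people who know the arm and who work under a protocol that expects no adverse events.

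4. **What the filter can detect.** In a child aged 4 to 7, a late-recognised illness looks like ordinary childhood illness. Few people would attribute a single case to a parent website. If there were an effect, it would appear as an excess in one arm. The harms section describes no arm comparison, and under {21a} the safety monitoring committee takes the place of a data monitoring committee.

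5. **What is already collected.** Under Table 2, the Medical history form (with child diagnoses) is completed at T1 to T5, and the Client Service Receipt Inventory (CSRI) at T1, T3, T4 and T5. Child pain, somatic symptoms, Rome IV items and quality of life are collected at T1 to T5. Section {11d} adds treatment received during the study. All of this is collected in both arms and does not depend on relatedness. None of it is designated as safety data or sent to the committee.

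6. **What Aim 3 sees.** Let U be the cost of unneeded care avoided in the SLCBT arm, N the cost of needed care not sought, and L the cost of any later care or lost parent time that results, all relative to EC. The observed saving is U + N − L. The rule uses only this net value. The same saving can arise with N = 0 or with N well above 0, and nothing in Aim 3 tells these apart.

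**The case against.** The strongest reply is that this is one loosely worded pair of sentences in a journal article. A full protocol exists (Trial status) and may define adverse-event forms, the relatedness assessment and the committee's tables. Section {22} also binds the investigators to the IRB's safety reporting requirements and lets the committee act on other safety issues. The study was classed as minimal risk, and children with daily chronic pain, painful gastrointestinal diagnoses or severe chronic disease are excluded. The module on when to act on possible illness may be a safeguard rather than a hazard. Hypothesis 3 compares child functioning and symptoms between arms. The proposed table has limits too: a count of new diagnoses does not show lateness, and missed illness could even lower the count.

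Much of this stands, and it rules out several stronger readings that a reader might infer:

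- **That adverse events are documented only if related.** The text does not contain that restriction, and the next sentence refers to all events. The fault is a contradiction, not a clear exclusion.
- **That delayed care would leave no record.** Diagnoses, symptoms, treatment and service use are collected in both arms regardless of relatedness.
- **That Aim 3 rewards delay outright.** It is a net cost. Expensive later care or lost parent time reported within the 18 months would count against the SLCBT arm.
- **That a particular number of harmed children would be missed.** The documents give no rate for late diagnosis or for attribution to the study, so any such number would be invented.

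What the reply does not remove is that the article states a documentation rule and then contradicts it. That is different from leaving a detail to the full protocol.

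**Conclusion.** The point holds in a limited form and is worth correcting. Section {22} makes documentation depend on believed relatedness while promising review of all adverse events, and the two must be reconciled. A relatedness filter, with arm-aware coordinators in contact with families, is a weak means of detecting late-recognised child illness. Aim 3 does not separate unneeded from needed care, although data that would help interpret it are already collected in both arms.

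The size cannot be quantified from the documents. The conclusion rests on two judgements: that late recognition is a plausible unwanted effect of training parents to respond less, and that single cases would rarely be attributed to the website. It does not rest on any evidence that such harm will occur.

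**What to change.** 1. Reword {22} so that adverse events are documented in both arms whatever their judged relatedness. Record relatedness as an attribute of the event, not as a condition for entry, and make the weekly review and the committee reports refer to the same set of events.
2. For the safety monitoring committee's quarterly review, tabulate by coded arm the new child diagnoses (Medical history form, T2 to T5) and the service use reported on the CSRI (T3 to T5). Use whatever service categories the form contains; the article does not show that emergency visits or admissions are itemised.
3. Report the same table beside the Aim 3 result as descriptive context. State that it has limited power at 460 / 2 = 230 families per arm and that it does not measure delay directly. An absence of difference should not be presented as proof that no needed care was missed.

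The cost is a wording change and a little more documentation and reporting work each quarter. The table uses data already planned, so no new assessment is needed.

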### Frequency and plans for auditing trial conduct {23}

Data quality will be ensured by annually verifying investigator compliance with all human subjects and HIPAA requirements. Additionally, Seattle Children’s Hospital’s Office of Research Compliance performs regular audits on all research studies. Furthermore, automated rules and logic in the study tracking database will enforce compliance with IRB requirements, conformance with informed consent requirements, and adherence to study protocols.

### Plans for communicating important protocol amendments to relevant parties (e.g., trial participants, ethical committees) {25}

Any protocol modifications will be updated on ClinicalTrials.gov as needed and in the participants’ consent forms if participant activities are affected. All modifications will additionally be communicated to the study team (including co-investigators) and IRB for approval prior to implementation.

## Dissemination plans {31a}

Study results will be disseminated via publication in peer-reviewed journals, reporting on ClinicalTrials.gov within 12 months of study completion, and presentations at professional society meetings. No identifying images or other personal or clinical details of participants will be presented in reports of the trial results. A summary of the study findings will be sent via email to all study participants after the final trial endpoint completion.

## Discussion

This intervention moves a previously successful parent training program for children who were diagnosed and treated for FAPD upstream to test whether it can be used to prevent precursors to future development of FAPD among children who are at risk by virtue of their parent’s experience with IBS. It will be the first study to evaluate the potential benefit of an early preventive psychosocial intervention specifically for children at risk for a common pediatric pain condition. The online aspect of the intervention being tested is also a significant advantage and significantly increases accessibility across many population groups.

### Limitations

There are several potential limitations to consider. First is the risk of drop-out. Participants may not complete all follow-up assessments. Efforts to retain study participation over 18 months of follow-up assessments include maintaining regular contact through several forms of communication (e.g., text, email, phone), sending birthday cards to children, and reminders of upcoming assessments. Second, recruiting parents into family-based preventive programs is well known to be challenging, and rates of community-wide recruitment into universal parenting programs are typically less than 20% [69–71]. However, the pervasiveness of social media in the US and Canada [72, 73] and the ease and constancy of access via mobile devices make Facebook [74, 75] and other outreach mechanisms (e.g., Twitter, Reddit) valuable tools to increase successful recruitment of participants to research studies [76–83]. Finally, there is the potential that our findings may not generalize to some populations. Our program is only available in English, and some groups may not have access to, or be comfortable with web-based interventions of this kind. If successful, it is our expectation that other delivery formats of this program will be developed.

### Strengths

The preventive REACH intervention is based on a growing body of literature that demonstrates the effectiveness of a SLCBT intervention in helping children with established chronic pain. The intervention is delivered by web and mobile technologies, which make it easily scalable for wide dissemination. Many parents do not have access to in-person psychological services or experience other significant barriers to seeking services, particularly in low income and rural areas. Access to internet and smartphone technologies is high, even among those of low income. According to a Pew Research Center Internet Survey, 98% of adults ages 30–49 years use the internet regularly (including 91% of Black adults and 97% of Hispanic adults) [84]. Our plan to use these technologies to deliver treatment allows us to potentially also reduce disparities in care. Thus, this research reflects a practical approach to prevention. Our focus on economic costs is innovative, providing data to address the potential cost-savings of SLCBT intervention in reducing health care costs and indirect costs of parental missed work time. Our community recruitment approach provides an efficient way of reaching a broad but targeted population of parents with IBS and greatly increases external validity.

In conclusion, if successful, this study has the potential to provide a model for a preventive intervention for a wide range of pediatric health problems which can impact functioning beyond early childhood in which parental responses are influencing factors. This early intervention may avoid a lifetime trajectory of disability and its associated costs.

### Trial status

Recruitment started on October 11, 2023. The current approved protocol is version date 9/1/2023 (submission approval date: 9/27/2023; approved version at final journal submission: 9/1/2023). Recruitment is estimated to be complete by April 2027. Any protocol modifications will be updated on ClinicalTrials.gov and on the participants’ consent form if required.

## Data Availability

The datasets that will be generated by this study will be made available in the Eunice Kennedy Shriver National Institute of Child Health and Human Development (NICHD) data repository DASH (https://dash.nichd.nih.gov/)

## Abbreviations

SLCBT: Social learning and cognitive behavioral therapy
EC: Educational web-based safety comparison condition
FAPD: Functional abdominal pain disorder
HRQOL: Health-related quality of life
RCT: Randomized controlled trial
REACH: REsilient Active CHildren
SCH: Seattle Children’s Hospital
REDCap: Research Electronic Data Capture
IBS-SSS: Irritable Bowel Syndrome Symptom Severity Scale
ARCS: Adult Responses to Children’s Symptoms
GAD-2: Generalized Anxiety Disorder scale
PCS: Pain Catastrophizing Scale
PANAS: Positive and Negative Affect Schedule
MSPSS: Multidimensional Scale of Perceived Social Support
CSSI-8: Children’s Somatic Symptoms Inventory
PedsQL-SF: Pediatric Quality of Life Inventory—Short Form
CSRI: Client Service Receipt Inventory
TEI-SF: Treatment Evaluation Inventory—Short Form
MICE: Multiple Imputations with Changed Equations
MEPS: Medical Expenditure Panel Survey
SMC: Safety Monitoring Committee
